### 5.6.1 Early study suspension

If the study must be interrupted prematurely, all non-used materials should be returned to the sponsor. The principal investigator will keep the investigator file and the completed CRF.

In case there were no patients included in the study, the sponsor will take care of all materials.

## 5.7 SOURCE DATA

Source documents are the patient's medical records including routine laboratory results obtained from blood tests. Also specific forms such as RMD and MVA.HIVconsv administration forms (attachments B and C), SERAD questionnaire (attachment D), PK form (attachment W) and MAP Phase Monitoring Form (attachment E) will be considered source documents. A scanned copy of all source documents will be included in the patient's medical chart, when possible; in all cases, these source documents will be included in the investigator site file.

Study data will be collected through an electronic Case Report Form (eCRF).

All investigational results from analysis performed from stored samples (virological, immunological results as well as PK determinations) will be recorded in electronic databases. Once the trial is finished, all databases will be unified.

Information regarding safety and tolerability of MVA.HIVconsv vaccinations and RMD administration will be collected using a patient diary (attachments F and G) which will be reviewed by the attending physician for grading and assessment of causality/imputability.

## 6 TRIAL INVESTIGATIONAL PRODUCT(S)

### 6.1 EXPERIMENTAL TREATMENT

Two investigational medicinal products (IMP)s will be tested in this trial:

- Vaccine MVA.HIVconsv 2x10^8 pfu, an investigational immunological product (vaccine) from a biological / biotechnological origin that contain genetically modified organisms.
- Romidepsin (Istodax®) 5mg/m^2, administered after antiemetic ondansetron 8mg intravenous (iv) infusion.

### 6.2 SUPPLY, PACKAGING, LABELING AND STORAGE

All investigational products will be stored at the Pharmacy Service of Hospital Universitari Germans Trias i Pujol, where reception, units, batch number and expiration date will be confirmed. No conditioning nor labelling will be required in the Pharmacy Service, except in case expiry date were to be extended for MVA.HIVconsv.

#### 6.2.1 Romidepsin (RMD, Istodax®)

RMD is a potent HDACi approved in the US for the treatment of cutaneous T-cell lymphoma (CTCL) in patients who have received at least one prior systemic therapy and peripheral T-cell lymphoma (PTCL) in patients who have received at least one prior systemic therapy whose marketing-authorization holder in Europe is Celgene Ltd. In Spain, RMD has only been used in clinical trials on hematology/oncology field under the investigation new drug application (PEI 07047). In the HIV field, RMD has been proposed as a potent HIV LRA.

RMD will be supplied by Celgene Ltd under a CTA in the form distributed by the technical director responsible for the development and control of the investigational product. RMD will be sent to the Pharmacy Service of Hospital Universitari Germans Trias i Pujol, labelled for its use (only for BCN02-Romi trial).

Storage is to be performed in a safe place at 20°C to 25°C, excursions permitted between 15°C to 30°C.

Preparation will be performed at the Pharmacy Service by the study pharmacist and according to manufacturer indications.

#### 6.2.2 MVA.HIVconsv

The MVA.HIVconsv is a non-marketed vaccine, and will be supplied by the University of Oxford under a CTA in the form distributed by the technical director responsible for the

development and control of the investigational product. MVA.HIVconsv has been manufactured by IDT Biologika GmbH in Germany. Storage is to be performed in a safe place at -80°C, excursions permitted between -60°C and -90°C.

### 6.3 DOSE, INTERVAL, ROUTE AND METHOD OF ADMINISTRATION

Administration of MVA.HIVconsv and romidepsin will be performed in the Unitat Polivalent d'Investigació Clínica (UPIC) from Hospital Universitari Germans Trias i Pujol.

#### 6.3.1 Romidepsin (RMD, Istodax®)

Dose: 5mg/m^2 over 4hours  
Interval: weeks 3, 4 and 5

##### Method of administration:

Romidepsin is a cytotoxic drug and will be used with appropriate handling procedures. Study staff will follow specific Standard Operating Procedure for the handling, preparation, administration and disposal of romidepsin (attachment H) for the BCN02-Romi trial.

Briefly, RMD will first be reconstituted with the supplied diluent and further diluted in 500ml 0.9% Sodium Chloride Injection, using proper aseptic technique at the Pharmacy Service to deliver the desired dose.

Before administration at the UPIC, the drug will be inspected visually for particulate matter and discoloration. Romidepsin will be infused over 4 hours intravenously using an IV infusion pump.

According to investigator's brochure, patients will also receive antiemetic treatment before (ondansetron 8mg ev) and for 3 days after the infusion (8mg every 12hours, oral, starting on day of RMD administration).

Patients will be admitted on the night before the first RMD (RMD1) infusion for a clinical and laboratory blood work and will be observed for the following 24hours. On RMD2 and RMD3, patients will be admitted at the UPIC on the morning of RMD infusion and will be observed for 12hours.

Data will be logged in a specific form (attachment B).

#### 6.3.2 MVA.HIVconsv

Dose: 2x10^8 pfu

Interval: weeks 0 and 9.

Method of administration: Study staff will follow specific Standard Operating Procedure for the handling, preparation, administration and disposal of vaccines (attachment I) for the BCN02-Romi trial.

Briefly, MVA.HIVconsv will be thawed until completely liquid in a biological level 2 (BL2) safety hood. The vial will not be shaken and the required volume will be drawn into the appropriate syringe. MVA.HIVconv will be administered within 1 hour of thawing. MVA.HIVconsv will be administered by intramuscular injection. MVA.HIVconsv will be administered into deltoid regions of both arms. The injection site will be observed for 30 minutes.

Data will be logged in a specific form (attachment C).

## 6.4 EXPERIMENTAL DRUG ACCOUNTABILITY

During the study, an accountability log, dispensing log and log of used vials will be kept for all IMPs. These logs will be monitored according to Good Clinical Practice (GPC) guidelines.

## 6.5 ARM DESCRIPTION

All patients will receive same experimental treatment, consisting of: MVA.HIVconsv vaccine administered 3 weeks before RMD1 infusion and 4 weeks after RMD3 infusion. Romidepsin infusions will be at weeks 3, 4 and 5 after first MVA.HIVconsv vaccine administration.

## 6.6 CONCOMITANT TREATMENTS

### 6.6.1 Ondansetron

Ondansetron is a marketed drug stated "generic" in Spain which is administered on a routine bases before the start of a potentially emetogenic chemotherapy. It will be supplied by the sponsor in the marketed form for iv (ondansetron 2mg/mL injectable solution) and oral (ondansetron 8mg tablet) administrations.

Ondansetron does not have particular temperature conservation, but vials should be in the exterior package to protect them from light. Ondansetron will be administered 30 minutes before RMD infusion (8mg iv) and during 3 days after the infusion (8mg tablet every 12 hours orally, starting on the day of RMD administration).

Preparation will be performed at the UPIC by the study nurse according to manufacturer indications. Once the product is diluted, infusion is to be performed in the next 24 hours and vial conserved between 2°C and 8°C.

### 6.6.2 cART

All individuals included will be under cART. To avoid drug interactions with romidepsin, all individuals will be on a regimen based in a non-boosted integrase inhibitor (raltegravir or dolutegravir based regimen). It is not expected any modification in the cART regimen all over the trial. In addition, a closely monitored antiretroviral pause is planned to offer cART resumption as soon as viral rebound is detected. A genotypic resistance test will be performed once viral rebound is confirmed to be >2,000 copies/ml. cART resumption regimen is expected to be still based on raltegravir or dolutegravir because neither raltegravir nor dolutegravir have an extended half-life that could favor the emergence of drug resistance short after treatment interruption, but new regimen decision will be to physician discretion.

### 6.6.3 Other

All other treatments administered during the study period will be considered concomitant treatments and should be documented in the CRF.

All participants will be discouraged to initiate any concomitant treatment without the knowledge and permission of the investigator. RMD is metabolized by CYP3A4. Patients will be discouraged of taking strong CYP3A4 inhibitors (ritonavir, cobicistat, atazanavir, ketoconazole, itraconazole, voriconazole, clarithromycin, telithromycin) or CYP3A4 inducers (nevirapine, efavirenz, etravirine, rifampicin, rifabutin, carbamazepine, phenytoin, phenobarbital, St. John's Wort) from 2 weeks before RMD1 until 2 weeks after RMD3.

All participants will be discouraged to receive any vaccination (including Hepatitis B, Pneumococcal and Flu vaccinations among others) within 2 weeks of study entry and along the duration of the trial.

### 6.6.4 MODIFICATION OF THE ANTIRETROVIRAL TREATMENT REGIMEN

## 6.7 COMPLIANCE

MVA.HIVcons and RMD compliance is guaranteed because study medication is to be administered by designated study nurse.

Antiretroviral treatment adherence will be self-reported by the patient by answering the adapted SERAD questionnaire (attachment D). No pill count will be performed to assess compliance. Ondansetron intake will be recorded in the diary card after each RMD administration (attachment G).

During the MAP period where cART is discontinued, plasma samples will be stored for future drug levels analyses for cases where antiretroviral consumption shall be suspected.

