  - 2.5. *In vivo* CTL toxicity assessment based on the most relevant marker from Endpoint 1 (viability, activation, ex) before RMD infusion and after 24 and 72h (RMD1), 12 and 72h (RMD2) and 12, 72 and 7 days (RMD3)
  - 2.6. Development of a population PK/PD analysis to integrate pharmacokinetics of RMD and *in vivo* observed effects of RMD
3. To evaluate the immunogenicity of booster vaccinations with MVA.HIVconsv before and after RMD administration and the effect on viral rebound control after discontinuation of cART.
    - 3.1. To evaluate immunogenicity of booster vaccinations, HIVconsv-specific T cell responses will be measured before, 1, 4 and 8 weeks after both booster vaccinations (MVA1 and MVA2) by IFN $\gamma$  ELISPOT using peptide pools covering different HIV proteins and HIVcons sequences. Total HIVconsv magnitude as well as HIVconsv focus over the rest of HIV-1 specific responses will be compared over time. These results will enable the futility analyses (see section 5.6)
    - 3.2. Evaluation of the effect MVA.HIVconsv boost vaccinations on viral suppressive capacity of CD8+ T cells in vitro, using a flow cytometric assay 4 weeks after MVA2.
    - 3.3. Determine the proportion of individuals who initiate a MAP following the futility analysis
    - 3.4. Determine the proportion of individuals who maintain sustained pVL <2,000 copies/ml during the first 12weeks after treatment cessation.
    - 3.5. Determine the proportion of individuals in whom cART is reinitiated due to viral rebound (2 consecutive pVL >2,000 copies/ml 3-5 days apart), >50% drop in CD4 cell counts, <450 cells/mm^3 and/or symptomatic acute retroviral syndrome.
    - 3.6. Evaluate the emergence of viral resistance during MAP phase
    - 3.7. Evaluate the viral suppression rates 6 months after treatment resumption.

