  - Plasma and PBMC storage following scheme detailed in attachment K
  - Discussion on treatment resumption once results from Biochemistry, Hematological parameters and CD4 cell count are available (72h): recommendation on cART resumption will be assessed based on clinical visit, willingness of patients to resume treatment, detection of viral load in the qualitative test and/or drop in CD4 cell counts.

After the first 12 weeks post-MAP (from W30):

- Fortnightly visits will be performed, including:
  - Qualitative viral load test (Xpert HIV-1 Qual de Cepheid)
  - Clinical visit, adverse event register
  - Reporting of symptoms suggestive of acute retroviral syndrome (including its severity grade)
  - Discussion on treatment resumption: recommendation on cART resumption will be assessed based on clinical visit, willingness of patients to resume treatment and detection of viral load in the qualitative test.
- Monthly:
  - Biochemistry and hematological parameters, viral load and CD4 count (performed at an external Lab)
  - Plasma and PBMC storage following scheme detailed in attachment K
  - Discussion on treatment resumption once results from Biochemistry, Hematological parameters and CD4 cell count are available (72h): recommendation on cART resumption will be assessed based on clinical visit, willingness of patients to resume treatment, detection of viral load in the qualitative test and/or drop in CD4 cell counts.

|                                                                                                           | Phase 2 (to be performed at BCN-Checkpoint) |    |    |    |    |    |    |    |    |    |    |    |                                                                |    |    |    |    |    |    |    |    |    |    |    |    |    |    |    |    |    |    |    |    |    |  |  |  |
|-----------------------------------------------------------------------------------------------------------|---------------------------------------------|----|----|----|----|----|----|----|----|----|----|----|----------------------------------------------------------------|----|----|----|----|----|----|----|----|----|----|----|----|----|----|----|----|----|----|----|----|----|--|--|--|

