### 10.1 RESPONSE EVALUATION (EFFICACY)

Two main efficacy endpoints will be evaluated in the BCN02-trial as follows:

Part A) Efficacy of the combined intervention (Kick & kill strategy) in the reduction of viral reservoir will be expressed by total HIV-1 DNA copies per million purified CD4+ T cells measured by quantitative digital droplet PCR (ddPCR) at baseline and 1 week after 3rd dose of RMD. Wilcoxon signed rank test will be used for comparisons.

Part B) Efficacy of HIVconsV vaccines in combination with RMD on viral rebound containment after treatment interruption will be evaluated by analysing the proportion of individuals who maintain sustained pVL <2,000 copies/ml at week 29 (12weeks after treatment cessation). Complementary, a survival analysis will be performed to describe time to rebound during the MAP period. Taking into consideration recent published data suggesting that early treatment initiation could favor a delayed viral rebound/spontaneous viral control in 10% in opposition to <5% in chronically-treated individuals, a positive efficacy signal has been established if at least >20% of individuals remain with pVL <2,000 copies/ml at w12 of MAP (pre-defined efficacy threshold).

Regarding virological and immunogenicity endpoints: Differences in the breadth and magnitude of different virological and immune parameters analyses between two longitudinal determinations in the same individuals will be assessed using a Wilcoxon signed-rank test. Correlations between the virologic, immune parameters and clinical outcome will be performed using Pearson test.

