### 10.3 SAMPLE SIZE DESCRIPTION

Individuals that participated in the BCN01 trial and which are followed in the extension phase (BCN01-RO) will be offered to participate in the study. Therefore, the trial will enroll a maximum number of 24 subjects. The primary endpoint of the study is safety and tolerability of the combined kick & kill strategy in recently HIV-1-infected individuals under early suppressive therapy. In terms of total number of individuals exposed to each MVA.HIVcons vaccine and confidence intervals to detect an AE (i-e- based on published results the probability of experiencing a grade 3 or 4 AE is thought to be <0.1). Information on expected rates of AEs related to RMD at the clinical dose proposed is still scarce. The trial has been designed as a pilot study and will only allow detection of a large effect among participants. However, the incidence of grade  $\geq 3$  or SAEs will be used as a measure of safety of the experimental strategy.

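### Drug levels during the treatment pause are tied to suspicion, so a covert cART user who stays suppressed would be scored as a viral controller unless someone suspected it

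*Protocol*

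**What the plan says.** Section 6.7 (Compliance) covers drug exposure during the pause in one sentence: "plasma samples will be stored for future drug levels analyses for cases where antiretroviral consumption shall be suspected". Storage is general, but the stated purpose of assay is limited to suspected cases. The section does not define suspicion or say who judges it. On cART generally it adds: "No pill count will be performed to assess compliance".

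Control is defined by viral load alone. Endpoint 3.4 in section 5.3.2 reads: "Determine the proportion of individuals who maintain sustained pVL <2,000 copies/ml during the first 12weeks after treatment cessation". Section 10.1, Part B, sets the decision rule: "a positive efficacy signal has been established if at least >20% of individuals remain with pVL <2,000 copies/ml at w12 of MAP". Neither makes verified absence of cART a condition, and neither says how a participant found to have taken cART is counted.

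The SERAD adherence questionnaire is listed at the visit that opens the pause (8.1.14) and again after cART resumption (8.2 and 8.2.1). It is not listed in MAP phase monitoring (8.1.15) or at the resumption visit (8.1.16). The visit table in 8.1.15 has a concomitant-treatment row. The text of 8.1.15 adds "Plasma and PBMC storage following scheme detailed in attachment K" to the visits at weeks 2, 4, 8 and 12 of the pause, and monthly after that.

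**The concern.** A claim of control off treatment is only as good as the evidence that participants were off treatment. The most visible sign of undisclosed cART is that the virus does not rebound, and that is also the success outcome. If testing waits for suspicion, the apparent successes are checked only where someone doubts them. The trial is open-label with a single arm (5.1), so no comparator group would carry the same error and cancel it.

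The error runs in one direction. Covert use either leaves the count of controllers unchanged or raises it. It can also lengthen the time to rebound. In the correlates-of-control analysis (10.1) it would label someone still on drug as a controller. Section 3 intends those correlates to help select people for future treatment interruptions, so mislabelled outcomes there would carry beyond this trial.

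**Working it through.** The protocol derives no power or error rate from the 20% threshold, so there is no stated figure to reproduce. The check asks what one covert user does to the protocol's own decision rule.

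**Inputs from the protocol**
- Reference rate p = 0.10, from section 10.1: "delayed viral rebound/spontaneous viral control in 10% in opposition to <5% in chronically-treated individuals".
- Signal rule: more than 20% below 2,000 copies/ml at week 12 of the pause (10.1), read as strictly more than 20%.
- Size, from section 10.3: "the trial will enroll a maximum number of 24 subjects".

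**Assumptions**
- The number entering the pause is not stated. I use n = 24 (the maximum) and n = 15 (illustrative).
- One covert user who is certain to stay below 2,000 copies/ml. The protocol gives no rate of covert use.

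**Counts needed**
- n = 24: 20% is 4.8, so r = 5 (5/24 = 20.8%).
- n = 15: 20% is exactly 3, so r = 4 (4/15 = 26.7%).

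**Formulas**
- No covert user: P(X ≥ r), with X ~ Bin(n, 0.10).
- One covert user counted as a controller: P(X ≥ r − 1), with X ~ Bin(n − 1, 0.10).

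**Results, n = 24**
- None: 1 − (0.0798 + 0.2127 + 0.2718 + 0.2215 + 0.1292) = 1 − 0.915 = 8.5%.
- One: 4 or more of the other 23 are needed; 1 − (0.0886 + 0.2265 + 0.2768 + 0.2153) = 1 − 0.807 = 19.3%.

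**Results, n = 15**
- None: 1 − (0.2059 + 0.3432 + 0.2669 + 0.1285) = 1 − 0.944 = 5.6%.
- One: 3 or more of the other 14 are needed; 1 − (0.2288 + 0.3559 + 0.2570) = 1 − 0.842 = 15.8%.

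**Range over the unknown rate.** Suppose instead that each participant has probability c of covert, fully suppressive use. The apparent control rate is then c + (1 − c) × 0.10.

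| c | apparent rate | n = 15 | n = 24 |
|---|---|---|---|
| 0 | 0.100 | 5.6% | 8.5% |
| 0.02 | 0.118 | 9.1% | 14.5% |
| 0.05 | 0.145 | 16.2% | 26.2% |
| 0.10 | 0.190 | 31.5% | 49.0% |

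One person is worth 100/24 = 4.2 percentage points at n = 24 and 100/15 = 6.7 at n = 15. The gap between the reference rate and the threshold is 10 points.

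**The case against.** The protocol foresees the problem and banks samples for it, and it does not exempt apparent controllers from testing. A reader might infer that hopeful investigators will choose which successes to leave unchecked. The text does not support a statement about motive, because section 6.7 names no decider. A laboratory plan or SAP could treat non-rebound as grounds for suspicion without contradicting it. What stands is that the rule, as written here, makes testing discretionary exactly where the outcome is favourable.

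Nor does the pause go unrecorded. Concomitant treatment is recorded at the pause visits, other treatments go into the CRF (6.6.3), and a dedicated monitoring form exists (Attachment E, not shown). Participants also have little stated reason to conceal use: their willingness to resume treatment is considered at each visit (8.1.15), and payment is not tied to control (13.3). These points lower the likely frequency of covert use. They do not replace a drug level, since every one of these records depends on disclosure.

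The arithmetic is conditional. It assumes a covert user who stays suppressed. Intermittent use need not suppress, and someone who would have controlled anyway adds no false success. One false controller changes the declaration only when the count falls exactly at the cut-off. Rebound is also a secondary endpoint (5.2) in a pilot trial, although 10.1 calls it one of two main efficacy endpoints and attaches a pre-defined threshold.

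Finally, it is tempting to say that the evidence already sits unread in the freezer. Section 8.1.15 assigns the stored material to virological and immunological studies, and volumes depend on Attachment K, which is not shown. Spare plasma is plausible but not documented.

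**Conclusion.** The point holds as a weakness in how Part B verifies its outcome. Drug-level testing in the pause is tied to undefined suspicion, control is scored on viral load alone, and no other stated procedure objectively confirms that cART was stopped. A covert user who stayed suppressed would count as a controller unless someone suspected it, and the bias favours the intervention.

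One such user roughly doubles to triples the chance of a false signal: 8.5% to 19.3% at n = 24, and 5.6% to 15.8% at n = 15. These figures rest on the 10% reference rate, a strict reading of the threshold, an assumed number entering the pause, and an assumed user certain to stay suppressed. They show sensitivity to one person, not how likely covert use is. A reader should not infer that covert use is expected, or that any particular apparent controller would be false; the documents support neither. The plan should be changed because the check is cheap and the result is fragile.

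**What to change.** In section 6.7, replace the suspicion trigger for apparent controllers with an outcome trigger. For everyone scored below 2,000 copies/ml at week 12 of the pause, assay the participant's integrase inhibitor in the plasma stored at the pause visits (weeks 2, 4, 8 and 12 in the text of 8.1.15), before the efficacy signal is declared. Keep testing on suspicion for the others. Confirm against Attachment K that enough plasma is stored.

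State beforehand that a participant with drug detected beyond a pre-set washout time is not counted as a controller in endpoint 3.4, the time-to-rebound analysis or the correlates analysis. Report each result with and without such participants.

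The cost is a short text change and up to four assays per apparent controller, with no new visit. The control rate may come out lower. Two limits remain. Spot assays can miss intermittent use, the more so because section 6.6.2 notes that neither integrase inhibitor has an extended half-life. Someone who took cART early and rebounded before week 12 would still be tested only on suspicion, so time to rebound is only partly protected.
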